## Discussion

To the best of our knowledge, this is the first study to investigate the effectiveness of UP in a sample of young adults diagnosed with UHR who also have comorbid emotional symptoms. If the results of this study show that UP is effective in treating the comorbid symptoms of UHR for psychosis, this finding could contribute to expanding the psychotherapeutic approaches that can be used with young people presenting with an at-risk mental state. UP may be complementary and/or an alternative to standard CBT approaches. This study would need to be replicated with a bigger sample.

Unified protocol has been shown to be effective in patients with a primary diagnosis of emotional disorders, including cases with comorbidity, according to the systematic review studies and meta-analyses conducted to date (Sakiris and Berle, 2019; Cassiello-Robbins et al., 2020; Carlucci et al., 2021). We hypothesize that this intervention could be equally effective in young patients because there has not been a chronification of their symptoms yet.

The UP contents and the way each emotion regulation technique is introduced and trained for helps patients to normalize their emotional symptoms or disorders, because all people can experience intense emotions and respond with emotional behaviors. It is positive for all people to improve their emotional regulation skills. This perspective focused on training skills can also help to reduce mental health stigmatization. In addition, UP uses expressions like “emotional experiences,” “intense emotions,” and “emotion driven behaviors” instead of other terms like “aggressive response” or “negative emotions.” All these aspects can help reduce the rejection of treatment by mental health services, especially in young people.

The telematic group format of the UP could improve therapeutic adherence in young people, as they are familiar with new technologies (Lupton, 2021). Further, it may encourage the recruitment of patients residing in remote areas and those without specialized care resources.

Cognitive behavioral therapy delivered in TAU is an intervention that has already been shown to be effective in patients of this type (Van der Gaag et al., 2013a). However, significant differences are expected in clinical variables in those patients who additionally receive the intervention with the UP, mainly in comorbid emotional symptomatology.

Given the high comorbidity of emotional disorders in patients with UHR (Rutigliano et al., 2016) and the presence of errors in information processing in both groups of disorders, such as jumping to conclusion, selective care, and catastrophization, as well as avoidant behaviors (Livet et al., 2020), it is likely that these share common transdiagnostic mechanisms with ED. It may be the case that improving emotional regulation will have a positive effect on cognitive biases implicated in the onset and maintenance of both emotional disorders and symptoms of psychosis. If the results show positive associations between improved emotional regulation and improvement in cognitive biases, this would provide a strong theoretical and clinical basis for offering UP to people at the UHR of psychosis.

One limitation of the study is the potential difficulty in isolating the impact of UP on outcome measures. This study is a naturalistic study, that is, it is carried out in the context of public mental health, which is why it is comparable with what has been done up to now. Clinically, it would be more ethical to offer an intervention like UP to all the participants of the study. We expect that the statistical analyses mentioned above can increase the robustness of the study results and solve this limitation.

The UP has already been shown to be effective with similar symptoms (Sakiris and Berle, 2019; Cassiello-Robbins et al., 2020; Carlucci et al., 2021) and this brings us closer to the clinical reality of mental health services for young people in public health. Furthermore, this design may make it easier to collect more samples since this type of patient is not very prevalent. There are several previous studies that have used this type of methodology (e.g., Carl et al., 2014). In this sense, this would be the first step toward obtaining preliminary data on whether the UP adds something to what is already done and to assess aspects of viability and user satisfaction. The next steps will be to compare the UP in isolation with the TAU.

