## Materials and methods

### Study design

This study is a randomized controlled trial. All patients are assessed at baseline. Patients are assigned to either treatment group, one receiving immediate treatment with UP and treatment as usual, or to a waiting list, only receiving treatment as usual. All patients are assessed post-treatment and at 3-months’ follow-up. After the final assessment, patients in the waiting list are offered the UP. A list of random numbers created for this purpose is used.

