### Interventions

All study participants receive TAU, within our early intervention program. It includes the following interventions: psychological therapy (about 20–40 sessions of CBT) as well as psychiatric treatment (with antidepressants, benzodiazepines and only when needed antipsychotic medication), social work intervention (vocational orientation and support), nursing care (side effects monitoring and healthy habits), individual cognitive remediation (if necessary), and family therapy. The number of sessions received in TAU depends on the clinical status of each patient. The maximum duration of TAU is 5 years. CBT delivered in TAU consists of techniques such as behavioral experiments, socratic questioning, and some exposure techniques mainly focused on subthreshold psychotic symptoms (French and Morrison, 2004; Nelson and Orygen Youth Health Research Centre Issuing Body, 2012; Van der Gaag et al., 2013a). Patients receive weekly or fortnightly sessions of psychotherapy. UP includes establishment of the specific therapeutic aims of each participant, motivation techniques, emotional psychoeducation, teaching functional analysis of the emotional experiences, mindfulness techniques, cognitive flexibility, analysis of emotional behaviors, and training in opposite behaviors. We also use interoceptive exposure, which we never use in individual CBT, and we teach patients to create exposure hierarchies for intense emotions so that they can follow treatment without the continuous supervision of a therapist. The UP consists of 15 online group sessions of 2 h each week. The groups include 5–8 participants. Participants receive an additional follow-up session 1 and 3 months after the end of the program. The sessions work on the 8 modules of UP for the transdiagnostic treatment of emotional disorders, as detailed in the reference manuals (Barlow et al., 2019). A summary of each session of the UP is detailed in Supplementary Appendix C.

Fidelity to the UP treatment protocol is guaranteed through weekly supervision with an accredited therapist. In addition, the therapists who will perform the UP intervention have undergone a 20-h training course. The contents of each module are summarized in an infographic and delivered to patients after the UP session to improve adherence to the intervention and acquisition of the techniques.

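### The planned session-adjusted analyses cannot resolve the difficulty of isolating UP's effect; the trial supports only an add-on conclusion

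*Protocol article*

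**What the plan says.** Study design randomises patients to two arms, "one receiving immediate treatment with UP and treatment as usual, or to a waiting list, only receiving treatment as usual". Interventions confirms the common background: "All study participants receive TAU, within our early intervention program". That background includes CBT. On UP the same section says "The UP consists of 15 online group sessions of 2 h each week" and adds "Participants receive an additional follow-up session 1 and 3 months after the end of the program". On the intensity of the background treatment it says "The number of sessions received in TAU depends on the clinical status of each patient".

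Data analysis plans a linear mixed model. Its main effects are time, condition and number of sessions (CBT sessions within TAU, UP sessions and others). Its interactions include condition by time and condition by sessions by time, with type and dosage of medication also named. The section expects to find subgroups whose course differs by sessions received.

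The Discussion then names as a limitation that UP's impact may be hard to isolate, links this to the naturalistic public-service setting, and concludes: "We expect that the statistical analyses mentioned above can increase the robustness of the study results and solve this limitation". Earlier in the Discussion, on what a positive result could mean, it says "UP may be complementary and/or an alternative to standard CBT approaches". Near the end it says "The next steps will be to compare the UP in isolation with the TAU".

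**The concern.** The Discussion states a limitation and then, in effect, withdraws it by pointing to the statistics. The limitation comes from the design: one arm receives a package that the other does not receive at all in the comparison period, on a background whose intensity varies with how the patient is doing. A regression on session counts does not supply the missing comparison.

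At stake is how the results are reported. If the text stands, a coefficient from a session-adjusted model could be presented as UP's isolated effect. That coefficient would be neither randomised nor specific to UP content. It could also displace the condition-by-time contrast, which randomisation does protect.

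A smaller matter of consistency is the remark that UP may be an alternative to CBT. It sits uneasily with the later statement that UP in isolation is for a future study.

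**Working it through.** **Inputs.** From Interventions: 15 UP sessions of 2 h; follow-up sessions at 1 and 3 months (length not stated), read as two; about 20–40 CBT sessions in TAU, with no period given. From Study design and Interventions: no UP in the waiting-list arm until after the final assessment, about seven months on. From Sample size calculation: difference 1.57, SD 1.6, two-sided alpha 0.05, power at least 0.80, 20% loss, 21 per arm.

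**The plan's own figure.** n per arm = 2 × [1.6 × (1.960 + 0.842) / 1.57]² = 16.30. Allowing for 20% loss, 16.30 / 0.80 = 20.38, rounded up to 21. The stated 21 per arm (42 in total) reproduces. Rounding to 17 before inflating, or using the t distribution (17.32 / 0.80 = 21.6), gives 22. Sample size is not at issue; 1.57 is used below only as a convenient effect.

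**Scheduled UP contact.** 15 × 2 h = 30 h in the immediate-UP arm and 0 h in the waiting-list arm during the comparison. With the two follow-up sessions the count is 17 against 0.

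**Can the model separate UP content from what comes with it?** Write the expected arm difference as S + C, where S is the effect of UP content and C the effect of group contact, therapist time and expectation.

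| S | C | Expected arm difference |
|---|---|---|
| 1.57 | 0 | 1.57 |
| 0 | 1.57 | 1.57 |
| 0.785 | 0.785 | 1.57 |

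The rows cannot be told apart. Each UP session attended delivers content and contact together, so a per-session slope does not separate them either. More patients would not help.

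**What happens when UP sessions enter the model beside condition?** If all UP patients attend the same number, the two variables are perfectly collinear. Otherwise the condition coefficient is a contrast at equal numbers of UP sessions. For controls that number is zero, so the contrast is an extrapolation to UP patients who attended nothing. To show the scale, assume mean attendance of 13 of 15 sessions (capped at 15) with 21 per arm. These attendance figures are not in the documents. The variance inflation factor is 1 / (1 − r²), computed from unrounded r.

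| Assumed SD of attendance before the cap | Correlation r with arm | Variance inflation factor |
|---|---|---|
| 0 | 1 | infinite |
| 1 | 0.994 | about 86 |
| 2 | 0.983 | about 29 |
| 3 | 0.967 | about 15 |

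**What happens when TAU sessions enter the model?** They are counted after randomisation, and Interventions says they follow clinical status. If UP improves symptoms, it may reduce the TAU sessions needed. Comparing arms at equal TAU sessions then removes part of the effect and compares patients selected for different clinical courses. The direction and size of the resulting bias cannot be derived from the documents.

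**Substitution.** No arm receives UP without TAU, so 0 of 42 patients inform the use of UP in place of CBT.

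**The case against.** The best reply is that the limitation can be read more modestly. The Discussion ties it to a naturalistic setting, and Data collection and Interventions record medication changes and TAU sessions as control variables. On that reading the aim is to separate UP from variable concurrent care, not UP content from group contact, and the planned terms address it. This reading is plausible but does not rescue the claim. Concurrent care recorded after randomisation and driven by clinical status may be affected by UP, so adjusting for it does not resolve the difficulty either.

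Several other points stand in the plan's favour:

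- The wording is hedged: the authors state an expectation, not a certainty.
- Study aims already defines the objective as UP in addition to TAU against TAU. The Discussion calls the data preliminary and asks whether UP adds to existing care.
- A waiting list with TAU is a legitimate comparator for an add-on question. The absence of attention-matched contact is not in itself an error.
- The 30 h is scheduled UP time. A reader might take it as the net difference in contact between arms, but the documents do not say how many TAU sessions each arm receives in the comparison period.
- A reader might infer that the plan claims the trial will show UP can replace CBT. It does not. The remark follows a conditional sentence, says only that UP may be complementary, an alternative or both, and is followed by a call for replication in a larger sample. The complementary half is what the design tests.

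**Conclusion.** The statement that the analyses can resolve the limitation is wrong as written, on either reading of the limitation. The reasons are structural: UP exposure is zero in all controls during the comparison, and session counts are post-randomisation variables, which for TAU depend on clinical status. This rests on the article's description of the design and takes no UP to be given to controls before the final assessment. The inflation factors of 15 to 86 depend on assumed attendance and are illustrative only; the non-identification does not depend on them.

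The point is narrow. It would go too far to conclude that the randomised comparison is invalid. The condition-by-time contrast, without session adjustment, estimates the effect of adding the UP group programme to TAU. Sample size, endpoints and assessments are unaffected, and no figure changes. The remark about an alternative to CBT is a minor inconsistency with the Discussion's own statement of next steps.

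**What to change.** 1. In the Discussion, replace the claim that the analyses can resolve the limitation with a statement that it remains.
2. State that the conclusion rests on the randomised condition-by-time contrast, read as the effect of adding the UP group programme, including its scheduled contact, to TAU, compared with TAU and a waiting list.
3. Label models that include session counts as exploratory, and say that they do not estimate an isolated effect of UP.
4. Where UP is called a possible alternative to CBT, add that this trial does not test it, in line with the later sentence on next steps.

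The cost is wording and a less favourable claim. No patient, visit, measure or calculation changes.

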## Ethics statement

This study has been evaluated and approved by the Drug Research Ethics Committee (CEIm) of the Parc Sanitari Sant Joan de Déu. All participants are being provided with an information sheet explaining the objectives and procedure of the study as well as the confidentiality of the data collected. All participants are being asked in writing for their consent in accordance with the Declaration of Helsinki (WMA, 2013) and Law 14/2007 on Biomedical Research.

## Abbreviations

UP: Unified Protocol
UHR: Ultra-high Risk (for psychosis)
TAU: Treatment as Usual
ED: Emotional disorders
WL: Waiting list
